# Background Information and Scientific Rationale

## Background and Rationale

### The Problem

500,000 Ontario youth (20-30%) have ≥ 1 mental health disorder^1^, 75% without specialist treatment^1^, compromising the timely care essential for optimal outcomes. 28,000 Ontario youth wait 8-30 months for care^2^. 200,000 youth have no access to care. Youth make 1.35 million out-patient and 70,000 emergency mental health visits/year. Youth suicidal ideation/self-harm doubled in 3 years^2^ prior to the pandemic. While mental health emergency hospitalizations skyrocket among youth; other causes are declining or stable. The critical shortage of mental health clinicians compounds increased treatment demand.

Youth are immersed in social media, doing little physical activity^3^ – lifestyle choices impacting their physical and mental health. Only 17.5% of Canadian youth meet sleep, physical activity and screen time guidelines^4^, and we know that meeting healthy lifestyle guidelines is associated with enhanced mental health. Achieving physical activity recommendations in grade 5 decreased adolescent mental illness risk by 47%^5^. Meeting screen time guidelines decreased mental health risk by 25%^5^. Each additional lifestyle guideline met further reduced mental health risk^6^.

### Summary of Work to Date

Our review of the medical records for 102 youth receiving specialist mental health support at CHEO found lifestyle counselling was included within mental health treatment for 95% of patients. In response, the expertise of 10 youth inpatients, 10 youth outpatients, 10 parents and 10 clinicians defined their desired type of lifestyle support. The HEalthy Lifestyle Project (HELP) resources were then iteratively and collaboratively designed with 12 inpatients, 33 outpatients, 18 parents, 11 clinicians and 23 Indigenous youth and elders (CHEO REB#20 62X).

Our pilot study of the HELP e-intervention enrolled youth contacting 1Call1Click or on the CHEO waitlist for specialist mental health services (CHEO REB#21 85X). 42% of youth waiting for specialist mental health support were eligible. Student researchers were able to approach 62% of eligible youth and successfully recruited 35% (n=10/29) in 4 months. Youth/families/clinicians requested the HELP pilot study be expanded to include youth seeking or receiving mental health support, adding new partners to our team (i.e., YouthNet/Réseau Ado, CHEO Youth Forum, 1Call1Click central intake). 26% (6/23) of teens enrolled in the next four months, with 5/6 youth having complete data. Most who expressed interest but did not enroll found the study questionnaires daunting as they were required to complete them virtually without researcher support. 83% (5/6) of enrolled youth demonstrated good engagement and measurable improvements in emotional health and lifestyle behaviours aligned with resource use. HELP resource engagement improved **
[figure not shown]
**sleep scores by 13%, decreased screen time by 0.96 hours/day and increased physical activity by 26 minutes/day. These changes allowed youth to achieve the recommended sleep and physical activity behaviours and reduce excessive screen use by approximately 50%.

Legend: Positive change was lower score for Strengths and Difficulties Questionnaire.

### Summary of Relevant Literature

**Children and Adolescents with Mental Illness have Unhealthy Lifestyles**

Child and adolescent psychiatrists routinely see patients whose unhealthy lifestyle choices significantly contribute to their presenting symptoms of mental distress. There is compelling evidence that poor sleep habits^10^, increased duration of screen time^11^, and poor nutrition^12^ are associated with worse mental health outcomes, including the development of depression and anxiety. Historic treatments failed to address these problems as their impact on mental health was significantly underestimated by health professionals, patients and families^13^.

**Lifestyle Changes Can Enhance Mental Health**

Research supports the effectiveness of lifestyle change for enhancing mental health. Lifestyle improvements associated with mental well-being include regular physical activity, balanced nutrition, getting enough sleep, decreased screen time, being outdoors, and making contributions in the service of others. Exercise can be as effective as psychotherapy and medication for treating some depressive disorders^14^; small changes in sleep duration can improve emotional regulation^15^; and nutritional interventions can improve overall functioning^12^. Increasing screen time is associated with decreased mental well-being and increased anxiety and depression in adolescents^16^. Furthermore, improvements to lifestyle behaviours can improve physical health, self-esteem, and quality of life^12,14,15,17–21^ and there is evidence that the positive effect may be additive^22.^.

**Rationale for Lifestyle Change interventions**

Youth are immersed in social media and doing little physical activity – poor lifestyle choices that impact their physical and mental health. Reviewing 102 health records of youth (50♀) receiving specialist support at CHEO we found few met criteria for major psychiatric diagnoses. Nevertheless, during the first two visits over 90% were counselled about changing sleep, physical activity and/or screen time. That mental health specialists are addressing the need for lifestyle change in the first visits with virtually all adolescents is evidence of the importance of lifestyle behaviour assessment/change as part of mental health treatment. There is a need to study lifestyle change intervention effectiveness in youth with mental illness because such interventions offer affordable, enjoyable, rewarding, and stigma-free treatment options that have no/few side effects/complications, and can be done individually or with family^14^. Healthy behaviours and moods spread through social networks, providing an opportunity for multiplier effects of lifestyle change on other family members, friends and neighbours^23^.

**Virtual Interventions to Support Lifestyle Change**

While the link between healthy lifestyle habits and mental health is well established, lifestyle change interventions have not been sufficiently studied in youth with significant mental health symptoms^13^. Through this project we will evaluate the HELP lifestyle change e-resource formats among youth experiencing mental distress. The HELP e-resources are available virtually to provide youth with access to these supports whenever they are ready to engage, even while they wait for specialist mental health treatment.

### Study Rationale

Lifestyle behaviour change through intensive in-person support has a positive impact on mental health. However, the youth mental health crisis creates a clear need to identify novel, scalable lifestyle behaviour change supports that can meet high demand. HELP is not an education intervention, but a novel virtual, asynchronous and scalable step-by-step support for self-guided lifestyle behaviour change. Youth anxiety/depression scores improved in 16 exercise RCTs^24^. 73 youth studies found improved psychological distress, anxiety, depression, and emotional disturbance linked to physical activity^25^. Decreasing recreational screen time, particularly phone/tablet use, improved adolescent mental health^26^. Sleep difficulties both determine and result from of youth mental health issues^27^. Targeting youth insomnia (6 weekly sessions) significantly improved psychological distress. These studies provide clear evidence of the mental health🡪lifestyle behaviour link^5,25,28–30^ and the impact of lifestyle behaviours on emotional health.

Knowing that only 17.5% of Canadian youth meet sleep, physical activity and screen time guidelines^31^, our team collaboratively developed the interactive HEalthy Lifestyle Project (HELP) e-intervention modules. HELP implements an innovative mental health care model that targets the important gap in timely youth mental health care. HELP is designed to engage youth in a step-by-step behaviour change journey focused on decreasing screen time, increasing physical activity, and/or improving sleep. We hypothesize that immediate access to the HELP intervention will support both prevention and treatment; reducing disease burden and long conventional therapy wait times^32^. The youth-initiated HELP format provides many youth-focused benefits^33^ and shares our lived experience of youth mental illness and mental health care, lifestyle behaviour change, and e-health expertise. Lifestyle e-interventions are stigma-free, have few side effects, can be done alone or with family and enable self-help strategies^14^. They also offer easy access, greater reach, flexibility for individual needs, and relatively lower cost.

## Study Objectives

This study will evaluate the efficacy of 6 months of HELP e-intervention access with kinesiologist support in a randomized controlled trial to determine if the changes in emotional health (primary outcome) and lifestyle behaviours (secondary outcomes) differ from changes among youth with delayed intervention access (control condition). Sustainability of the intervention will be assessed for an additional 6 months. Participants will be youth 12-17 years of age who contact youth mental health services (1Call1Click). We will also evaluate the impact of the HELP e-intervention on the use of mental healthcare services, the need for mental health professional support of lifestyle behaviours and the association between self-reported and objectively measured lifestyle behaviours.

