### Research Questions

1. Do youth (12 to 17 years of age) who engage in the 6-month HELP e-intervention have a larger improvement in emotional health (measured by the Strengths and Difficulties Questionnaire) than youth who do not receive the intervention?
2. Does engagement in the HELP e-intervention improve lifestyle behaviour (physical activity, sleep or screen time)?
3. Are changes in emotional health and lifestyle behaviours sustained for at least 6 months after completion of the HELP e-intervention?
4. Do youth who engage in the 6-month HELP e-intervention utilize fewer mental healthcare resources, during and for 1 year following RCT participation, than youth who do not receive the intervention?
5. Do mental health professionals supporting youth who engage in the 6-month HELP e-intervention provide lifestyle behaviour support less frequently than for youth who do not receive the intervention?
6. Are self-reported (i.e., perceived) lifestyle behaviour changes (study questionnaire responses) aligned with objective measures of screen time (smartphone tracking) and sleep and physical activity (accelerometry) in a randomly selected sub-sample (1 of 3) enrolled participants?

We hypothesize that youth engaging in the HELP e-intervention will have improved emotional health and enhanced lifestyle behaviours in comparison to those receiving the delayed (post 6-months) intervention. We hypothesize that changes during the intervention will be maintained for an additional 6 months, and that self-reported measures will accurately reflect objective measurements. We hypothesize that youth engaging in the HELP e-intervention will require fewer youth mental health supports, and when supported will be less likely to require treatment directed at lifestyle behaviours.

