### Study Assessments

A researcher blinded to study group allocation will work with enrolled youth to complete all study assessments. The accurate/reliable study questionnaires include measures of emotional strength (Strengths and Difficulties Questionnaire)^34^, lifestyle choices (Youth Quality of Life-short form)^35^, readiness for behaviour change (Stages of Change Questionnaire^36^), and sleep (Adolescent Sleep Hygiene Scale)^37^, physical activity (Habitual Activity Estimation Scale)^38^, and leisure screen time (Adolescent Sedentary Activity Questionnaire)^39^ behaviours. All enrolled youth will complete all questionnaires at 0, 3, 6 and 12 months. As in our pilot study (REB #21 85X), the questionnaires (Appendix E) will be completed virtually using RedCAP, with automated scoring of the responses according to published methods. At each assessment, youth will be asked to voluntarily self-report age (years), gender (boy, girl, unkown, other, prefer not to answer), and their use of other mental health therapies (Appendix F). Study enrollment does not restrict access to or use of other mental health supports.

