The blinded researcher will also administer the objective measures of sleep, physical activity and lifestyle to a randomly selected sub-sample of participants. One in every three participants will be provided by mail with an accelerometer to wear for 7 days at the time of the 0 and 6-month assessments. Each selected youth will wear a tri-axial accelerometer (Actigraph GT9X-BT, 180 day memory) on a waist-worn belt, over the right hip, in the mid axillary line, 24 hours/day for 7 days^40^ in addition to completing the study questionnaires. The goal is 24 hour accelerometer wear for 7 consecutive days to capture both physical activity and sleep, and to minimize data loss (monitor forgotten, etc.). The Actigraph GT9X-BT ([www.theactigraph.com](http://www.theactigraph.com)) can be worn for swimming or bathing to a 1-metre depth. Sleep times and reasons for device removal will be recorded on a log sheet (Appendix G). A minimum of 10 hours of wear time per day during waking hours will be required so that established cut points^41^ can be used to calculate daily minutes of sedentary, light and moderate+vigorous activity. The ActiLife software (Version 6.13.5, Actigraph Inc.) also calculates sleep duration based on measurement epochs lacking movement. At least 3 weekdays and 1 weekend day of valid data will be required. Screen use will be measured by utilizing the social media tracking function in the smartphone owned by each participant^42^. The researcher will explain to each participant how to access the social media tracking function that is build into their smartphone. Participants will be asked to take a screen shot of their social media use each day at the time they go to bed and to share the screen shot with the research team. Participants who do not own a smartphone will not complete the objective measures of lifestyle behaviours.

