## Data Analyses

Data cleaning will be on-going throughout data collection. Initial data analyses of youth enrolled in the first 9 months of the RCT will be completed in months 15-20. Detailed analysis syntax and modeling will be retained for use in the final modeling/analyses when data collection is complete. Statistical significance will be set at p<0.05 for all analyses.

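### The Protocol hypothesises that self-report is accurate but names only an association as the evaluation; for sleep and screen time the paired measures cannot test accuracy at all

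*Protocol*

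**What the plan says.** Three parts of the Protocol bear on this comparison.

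- **Target.** Study Objectives lists "the association between self-reported and objectively measured lifestyle behaviours" among the things to be evaluated. Question 6 under Research Questions asks: "Are self-reported (i.e., perceived) lifestyle behaviour changes (study questionnaire responses) aligned with objective measures of screen time (smartphone tracking) and sleep and physical activity (accelerometry"). The hypothesis paragraph that follows is stronger: "self-reported measures will accurately reflect objective measurements".
- **Analysis.** The Statistical Plan describes no method for question 6. Data Analyses gives only the general rule "Statistical significance will be set at p<0.05 for all analyses".
- **Measures.** Study Assessments names the self-report instrument for "sleep (Adolescent Sleep Hygiene Scale"), whereas the accelerometer software "also calculates sleep duration based on measurement epochs lacking movement". For screen time, the questionnaire covers leisure screen time and the phone function tracks social media use. For physical activity, the accelerometer yields daily minutes by intensity. Summary of Work to Date reports pilot changes as "sleep scores by 13%, decreased screen time by 0.96 hours/day and increased physical activity by 26 minutes/day", so sleep is a score and the other two are in time units. The accelerometer procedure also includes a log: "Sleep times and reasons for device removal will be recorded on a log sheet".

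**The concern.** Accuracy is a claim about agreement: the self-reported change should be close to the measured change. Association is weaker, saying only that the two changes rise and fall together to some degree. If the wording in Study Objectives is followed, a significant correlation could be reported as support for the accuracy hypothesis even though it carries no information on the size of any over-statement.

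Sleep and screen time have a further difficulty. The paired measures are different quantities, so a weak correlation would not show that youth report badly, and a strong one would not show that they report accurately.

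The sleep, activity and screen time outcomes in the full sample are questionnaire-based, and youth in a wait-list design know whether they have access. A reader will therefore lean on the sub-sample when judging those outcomes.

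**Working it through.** **Is there a stated figure to reproduce?** No. The Protocol gives no sample size, power or agreement target for question 6.

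**Sub-sample size.** Sample Size Determination gives 122 youth with complete data and about 100 to 200 enrolled. One in three is selected:
- 122/3 ≈ 41
- 100/3 ≈ 33
- 200/3 ≈ 67

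Invalid wear at either time point and youth without a smartphone would lower these.

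**Smallest significant correlation.** Assuming a two-sided 0.05 level and a Pearson correlation, r_crit = t/√(n − 2 + t²), with t the 0.975 quantile on n − 2 degrees of freedom.

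| n | t | r_crit | shared variance |
|---|---|---|---|
| 33 | 2.040 | 0.344 | 12% |
| 41 | 2.023 | 0.308 | 9% |
| 67 | 1.997 | 0.240 | 6% |

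**Effect of biased reporting of change on r.** If self-reported change y becomes a + b·y for all youth, with b > 0, then r is unchanged. As a hypothetical case, suppose every youth reports exactly twice the true change. Then r = 1, yet a reported gain of 26 minutes/day would be a true gain of 13.

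**The same data judged by agreement.** With equal SDs and a uniform shift of k SD in reported change, Lin's concordance coefficient is 2r/(2 + k²).

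| shift k | concordance, r = 0.5 | concordance, r = 0.7 | correlation significant, n = 41, r = 0.5 |
|---|---|---|---|
| 0 | 0.50 | 0.70 | 92.5% |
| 1 SD | 1.0/3 = 0.33 | 1.4/3 = 0.47 | 92.2% |
| 2 SD | 1.0/6 = 0.17 | 1.4/6 = 0.23 | 92.9% |

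The last column comes from 5,000 simulated bivariate normal samples per row. The correlation test is unaffected, apart from simulation noise, while agreement falls to a third. The values of r and k are assumed; the Protocol gives none.

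**Bias that does not matter here.** Question 6 concerns change. A youth who over-states activity by the same number of minutes at 0 and 6 months has that amount subtracted out. What remains is proportional over-statement, or a shift in reporting between the two time points.

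**A shift in one arm only.** Assume equal arms, the same true change in both, and a 1 SD over-statement in one arm. The variance of y rises from 1 to 1 + 1/4, so r falls to r/√1.25 = 0.894r. A correlation of 0.5 becomes 0.447, still above 0.308. The pooled correlation does not show such a shift; the mean difference by arm would.

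**Precision of an agreement analysis.** The 95% CI half-width for the mean difference is t/√n times the SD of the differences.
- n = 41: 2.021/6.403 = 0.32 SD
- about 20 in one arm: 2.093/4.472 = 0.47 SD

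**The case against.** The strongest reply is that the Protocol states no correlation test and no decision rule for question 6. Association is one word in a summary of objectives, the method may sit in a statistical analysis plan that is not shown, and the word does not rule out an agreement analysis. Question 6 itself asks only about alignment, which is compatible with association. This stands in part. The absence of a method is not the point, and a reader should not infer that a significance test of correlation has been specified as proof of accuracy. What remains is that the Protocol fixes a hypothesis of accuracy and names a weaker evaluation for it.

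A reader might also infer that biased self-report would pass as accurate in some stated share of trials. The documents do not support that. The percentages in the working are ordinary power under assumed correlations, and at r = 0.3 and n = 41 the power is only about 48%.

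Two further objections hold. A blanket switch to agreement would fail for sleep and screen time. Log-sheet sleep times are not the questionnaire responses that question 6 asks about, so they cannot validate the hygiene score.

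Finally, no efficacy analysis is conditional on question 6, and the Protocol does not call the sub-sample a check on reporting bias in the trial. That use is an inference about how readers will treat it.

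**Conclusion.** The point holds in limited form. As worded, the evaluation cannot support the accuracy hypothesis for physical activity. The hypothesis cannot be tested at all for sleep or screen time with the named measures. The sleep conclusion rests on the instrument being reported as a score in the pilot, since its items are not shown.

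The firm figures are the significance thresholds: about 0.31 at 41 youth, and 0.34 to 0.24 for 33 to 67. The concordance and simulation results are illustrations under assumed correlations and bias. The tempting reading that any over-reporting would be hidden goes too far, because bias that is constant over time cancels in change scores.

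The primary outcome is untouched. The change is worth making because a stated hypothesis cannot be answered as written and the data for a better analysis of physical activity are already being collected.

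**What to change.** **Physical activity.** In Study Objectives and Research Questions, state agreement as the target for this behaviour only. Report the mean self-report minus accelerometer difference in 0-to-6-month change, in minutes/day, with its 95% CI and limits of agreement. Name the accelerometer intensity category that matches the questionnaire. Give the same figures by study group as description only, since each arm will have about 20 youth.

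**Sleep and screen time.** Limit both the hypothesis and the conclusion to association between the questionnaire and the objective measure.

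**Supplementary.** Compare log-sheet sleep times with accelerometer sleep duration, and state that this does not validate the hygiene-scale score.

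**Cost.** This takes a wording change and a standard analysis of data already planned. The price is that accuracy becomes harder to claim for physical activity, with a CI half-width of about 0.32 SD of the differences at 41 youth. It is no longer claimed for the sleep and screen time questionnaires.

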### Research Questions

1. Do youth (12 to 17 years of age) who engage in the 6-month HELP e-intervention have a larger improvement in emotional health (measured by the Strengths and Difficulties Questionnaire) than youth who do not receive the intervention?
2. Does engagement in the HELP e-intervention improve lifestyle behaviour (physical activity, sleep or screen time)?
3. Are changes in emotional health and lifestyle behaviours sustained for at least 6 months after completion of the HELP e-intervention?
4. Do youth who engage in the 6-month HELP e-intervention utilize fewer mental healthcare resources, during and for 1 year following RCT participation, than youth who do not receive the intervention?
5. Do mental health professionals supporting youth who engage in the 6-month HELP e-intervention provide lifestyle behaviour support less frequently than for youth who do not receive the intervention?
6. Are self-reported (i.e., perceived) lifestyle behaviour changes (study questionnaire responses) aligned with objective measures of screen time (smartphone tracking) and sleep and physical activity (accelerometry) in a randomly selected sub-sample (1 of 3) enrolled participants?

We hypothesize that youth engaging in the HELP e-intervention will have improved emotional health and enhanced lifestyle behaviours in comparison to those receiving the delayed (post 6-months) intervention. We hypothesize that changes during the intervention will be maintained for an additional 6 months, and that self-reported measures will accurately reflect objective measurements. We hypothesize that youth engaging in the HELP e-intervention will require fewer youth mental health supports, and when supported will be less likely to require treatment directed at lifestyle behaviours.

